# Individualized blood pressure management and postoperative organ dysfunction in older hip fracture patients: a study protocol for a single-center, randomized, controlled trial

**DOI:** 10.1186/s12877-026-07594-5

**Published:** 2026-05-02

**Keywords:** Older patients, Hip fracture surgery, Intraoperative hypotension, Individualized blood pressure management, Multiple organ system dysfunction

## Abstract

**Background:**

Postoperative organ dysfunction is a leading cause of death and disability following hip fracture surgery in older patients. Intraoperative hypotension is a major modifiable risk factor for this complication, yet the optimal management strategy to prevent it remains controversial. We hypothesize that an individualized blood pressure management strategy is superior to standard management in reducing postoperative organ dysfunction.

**Methods:**

This single-center, randomized, controlled trial will enroll 180 patients aged 65–85 years with hip fractures under general anesthesia. Eligible patients will be randomly allocated in a 1:1 ratio to the individualized management group (targeting systolic blood pressure within ± 10% of baseline) or the standard management group (reactive management, where intervention is initiated only if systolic blood pressure < 90 mmHg or decrease of > 30% from baseline). A universal mean arterial pressure target of ≥ 65 mmHg will be maintained for all patients. The allocated hemodynamic management strategy will be maintained throughout surgery and during the post-anesthesia care unit stay. The primary outcome is a composite of dysfunction in at least one organ system (respiratory, cardiovascular, renal, and neurological) within 7 days after surgery. Secondary outcomes include the components of the primary outcome, intraoperative variables (including hemodynamic management data, fluid balance, blood loss, and serum lactate levels), intensive care unit and hospital stay, and all-cause mortality within 30 days after surgery.

**Discussion:**

This randomized controlled trial aims to determine whether individualized blood pressure management reduces postoperative organ dysfunction more effectively than standard management in older hip fracture surgery patients. If proven effective, this proactive approach may represent a significant advance in clinical practice, moving from reactive hypotension correction to preventive stabilization, potentially reducing major complications, shortening hospital stays, and improving functional recovery. The results will provide important evidence to guide hemodynamic management during general anesthesia in this vulnerable population, contributing to standardized, evidence-based protocols for enhancing perioperative outcomes.

**Trial registration:**

Trial registration: Chinese Clinical Trial Registry, ChiCTR2400093838. Registered on 12 December 2024. This manuscript presents the study protocol; participant recruitment is ongoing and results will be reported upon trial completion.

**Supplementary Information:**

The online version contains supplementary material available at 10.1186/s12877-026-07594-5.

## Background

Hip fracture is a common and serious injury among older patients, associated with a one-year mortality rate as high as 30% [1]. Survivors often face long-term challenges, including multiple systemic complications, disability, increased risk of refracture, and substantial healthcare costs [2].

The anesthetic management of hip fracture surgery commonly involves either neuraxial or general anesthesia. While both are acceptable, general anesthesia is frequently preferred or necessitated in cases of patient agitation, anticoagulation, difficult positioning, or anticipated prolonged and complex surgery [3–5]. However, general anesthetic agents can induce significant arterial and venous vasodilation, reduce systemic vascular resistance, and cause hemodynamic instability [6]. These effects are compounded by the age-related impairment of cardiovascular autoregulation and a high prevalence of comorbidities, which collectively render older hip fracture patients particularly susceptible to intraoperative hypotension (IOH) [7].

IOH is a well-established risk factor for hypoperfusion of vital organs, leading to adverse outcomes such as postoperative delirium [8], acute kidney injury (AKI) [9, 10] and myocardial injury [11], ultimately worsening the prognosis. The prevalence of IOH in this population is high. A large UK study reported that 61.0% of older hip fracture patients experienced a mean arterial pressure (MAP) < 65 mmHg, and 91.3% had a reduction in systolic blood pressure (SBP) > 20% from baseline [12].

Despite its high prevalence and strong association with poor outcomes, there is no consensus on the optimal definition or management strategy for IOH. Current guidelines primarily recommend avoiding excessive hypotension (e.g., a > 30% decrease from baseline or an absolute SBP < 90 mmHg) and maintaining MAP ≥ 65 mmHg [13, 14]. This approach is inherently reactive, as treatment is initiated only after hypotension occurs. Furthermore, the fixed threshold of MAP ≥ 65 mmHg may not be optimal for all patients, as it fails to account for individual variations in baseline blood pressure and autoregulatory thresholds.

In contrast to this reactive approach, an emerging paradigm is individualized or preemptive blood pressure management, which aims to maintain SBP within a narrow range (e.g., ± 10%) of baseline. This strategy has shown promise in reducing postoperative organ dysfunction in patients undergoing major abdominal surgery [15, 16], suggesting that proactive stabilization may be superior to reactive correction. However, high-quality evidence from randomized controlled trials is lacking specifically in older hip fracture patients.

Therefore, we hypothesize that an individualized blood pressure management strategy (targeting SBP within ± 10% of baseline) will reduce the incidence of postoperative organ dysfunction compared to a standard management strategy (preventing SBP < 90 mmHg or a decrease of > 30% from baseline) in older patients undergoing hip fracture repair under general anesthesia.

## Methods

### Study design

This randomized controlled trial was approved by the Medical Ethics Committee of Qilu Hospital of Shandong University (No. KYLL-202406–008-2; October 9, 2024) and registered at the Chinese Clinical Trial Registry (ChiCTR2400093838, December 12, 2024). This study has been conducted since December 2024 and will be completed by June 2026 in accordance with the Declaration of Helsinki and the Standard Protocol Items for Randomized Trials (SPIRIT) guidelines. A total of 180 participants will be randomly assigned to either an individualized or a standard treatment group. The research pattern is shown in Fig. 1. The participant timeline is demonstrated in Table 1.

**Fig.1 Fig1:**
[figure not shown]
Simplified schematic of the trial design

**Table 1 Tab1:**
[figure not shown]
Timeline of the study

*Abbreviations:* *PACU* postanesthesia care unit, *SBP* Systolic blood pressure, *DBP* Diastolic blood pressure; MAP, Mean arterial pressure, *HR* heart rate, *BIS* Bispectral Index, *T* temperature, *SV* Stroke volume, *Hct* hematocrit, *NRS* numerical rating scale, *ICU* Intensive Care Unit

### Trial objectives

The primary objective of this study is to determine whether individualized blood pressure management reduces the incidence of a composite of organ dysfunction within 7 days after surgery compared with standard management in older hip fracture patients.

### Research objects

Older patients (aged 65–85 years) who are scheduled to undergo hip fracture surgery under general anesthesia.

#### Inclusion criteria

Age between 65 and 85 years;American Society of Anesthesiologists (ASA) grades I-III;Patients who are planning to undergo surgery for a unilateral hip fracture under general anesthesia;Provision of signed written informed consent from the patient or their legally authorized representative.

#### Exclusion criteria

Severe uncontrolled hypertension (SBP ≥ 180 mmHg or diastolic blood pressure [DBP] ≥ 110 mmHg) at rest before surgery;History of acute cardiovascular or cerebrovascular events (e.g., acute myocardial infarction, heart failure, acute cerebral infarction) within 30 days prior to surgery;Previous history of major neurological or psychiatric disorders that would preclude accurate assessment of postoperative delirium or cognitive function, including but not limited to: moderate to severe Alzheimer’s disease, Parkinson's disease, prior stroke with significant residual cognitive or functional deficit, or psychosis;Severe pre-existing organ dysfunction, defined as any of the following:Cardiac: New York Heart Association (NYHA) class IV heart failure or left ventricular ejection fraction (LVEF) < 30%.Respiratory: Home oxygen therapy for chronic obstructive pulmonary disease (COPD) or forced expiratory volume in 1 s (FEV1) < 50% of predicted.Hepatic: Child–Pugh class C liver cirrhosis.Renal: Estimated glomerular filtration rate (eGFR) < 30 mL/min/1.73m^2^ or on chronic renal replacement therapy (dialysis).Multiple fractures or other trauma;Requirement for any vasopressor or inotrope infusion at the time of screening or hospital admission for the hip fracture, regardless of duration or indication;Current participation in another interventional clinical trial;Inability to communicate effectively, or severe hearing/visual impairment preventing reliable outcome assessment.

#### Withdrawal criteria

Participant Initiated: Participants may withdraw at any time without penalty. Reasons will be documented if provided.Investigator Initiated: The principal investigator may discontinue a participant for:Major protocol deviation (e.g., unplanned change in anesthesia or surgery).Loss to follow-up (inability to complete the 7-day primary outcome assessment).A serious perioperative complication where continuation is not in the participant's best interest.A Serious Adverse Event (SAE) probably or definitely related to the intervention.Data Handling: The primary analysis will follow the intention-to-treat (ITT) principle. Data collected until withdrawal will be included unless consent for data use is explicitly revoked.

### Randomization and blinding

Eligible participants will be randomly allocated in a 1:1 ratio to either the individualized or standard management group. The randomization sequence will be computer-generated by an independent statistician using block randomization with varying block sizes (of 4 and 6), stratified only by age group (65–74 years vs. 75–85 years) to ensure balance across this key prognostic factor. To guarantee allocation concealment and balance between groups throughout the trial, sequentially numbered, opaque, sealed envelopes will be used. The envelopes will be stored by an independent coordinator and opened by the attending anesthesiologist immediately prior to anesthesia induction. Due to the nature of the intervention, the anesthesiologist performing the intervention cannot be blinded. However, participants, postoperative outcome assessors, and data analysts will remain blinded to group assignment throughout the trial.

## Intervention

### Preoperative interview

Within 24 h prior to surgery, eligible patients will undergo a comprehensive preoperative assessment. This includes evaluation of general status, medical history, physical examination, and laboratory results to determine ASA physical status and Clinical Frailty Scale (CFS) score. The study's purpose, procedures, risks, and benefits will be explained in detail to the patient and their legally authorized representative. Written informed consent for both routine anesthesia and trial participation will be obtained.

The reference blood pressure will be obtained under standardized, pain-stabilized conditions. On the day before surgery, after achieving effective analgesia (Numerical Rating Scale [NRS] score ≤ 3) with Flurbiprofen Cataplasms (initiated upon admission and supplemented with rescue opioids as needed), the patient will rest supine for 5 min. Three consecutive SBP measurements will then be taken at 2-min intervals. If the variation between any two readings exceeds 10%, the series will be repeated after an additional 5-min rest. The mean of three stable measurements will be recorded as the reference SBP.

### Intraoperative monitoring

Standard monitoring will be established upon operating room arrival. Prior to induction, advanced monitoring will be initiated with a radial arterial catheter under local anesthesia for continuous blood pressure monitoring and arterial blood gas sampling. The arterial line will be connected to a LiDCOrapid system (LiDCO Ltd., United Kingdom) for stroke volume (SV), stroke volume variation (SVV), cardiac index (CI) measurement to guide goal-directed fluid therapy (GDFT) and vasopressor titration. Depth of anesthesia will be monitored using the Bispectral Index (BIS). All arterial pressure (SBP, DBP, MAP) and heart rate (HR) will be recorded electronically, with values extracted every 5 min for subsequent analysis.

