### Anesthesia induction and intervention

After preoxygenation, general anesthesia will be induced with intravenous sufentanil (0.2–0.3 μg/kg), etomidate (0.1–0.2 mg/kg), and rocuronium (0.6 mg/kg). An i-gel supraglottic airway will be inserted, and mechanical ventilation will be commenced.

Hemodynamic management will begin immediately post-induction. In the individualized management group, a continuous peripheral intravenous infusion of norepinephrine (10 μg/mL) will be started at 0.02 μg/kg/min and titrated to maintain SBP within ± 10% of the baseline, with a maximum dose of 0.2 μg/kg/min. In the standard management group, intermittent intravenous boluses of norepinephrine (10 μg) will be administered as rescue therapy only if hypotension occurs (defined as SBP < 90 mmHg or a > 30% decrease from baseline). For all patients, the MAP will be maintained at ≥ 65 mmHg as a universal minimum target [17]. If target blood pressure cannot be maintained at the maximum dose, rescue therapy (e.g., dopamine 2–5 μg/kg/min or epinephrine 0.01–0.05 μg/kg/min) will be initiated based on real-time hemodynamic monitoring. Finally, an ultrasound-guided supra-inguinal fascia iliaca compartment block (S-FICB) with 35 mL of 0.25% ropivacaine will be performed on the surgical side for postoperative analgesia.

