### Secondary outcomes

The secondary outcomes encompass the components of the primary outcome, other postoperative clinical events (including systemic inflammatory response, infection, and thromboembolic events), intraoperative variables (hemodynamic data, fluid balance, and serum lactate levels), postoperative recovery measures (pain score, durations of ICU and hospital stay), and all-cause mortality within 30 days after surgery. More details are provided in the S2 Appendix.

Hemodynamic variables, collected from anesthesia induction until PACU discharge, will consist of the total dosage of norepinephrine administered; the incidence of intraoperative hypotension (defined as SBP < 90 mmHg or a decrease > 30% from baseline, or MAP < 65 mmHg); the total dosage of urapidil administered; the incidence of intraoperative hypertension (defined as SBP > 160 mmHg and/or diastolic blood pressure > 90 mmHg) [15]; and the occurrence and management of severe bradycardia (defined as heart rate < 40 beats per minute).

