## Discussion

This randomized controlled trial is designed to evaluate whether an individualized blood pressure management strategy (targeting SBP within ± 10% of baseline) can reduce postoperative organ dysfunction more effectively than a standard reactive management strategy in older patients undergoing hip fracture surgery under general anesthesia. The underlying mechanism is hypothesized to be through preemptive stabilization of hemodynamics, thereby minimizing exposure to IOH and maintaining personalized organ perfusion pressures tailored to individual autoregulatory thresholds.

The primary goals of anesthetic management in hip fracture patients are to mitigate postoperative complications and facilitate early recovery and functional rehabilitation [21]. IOH is a well-established, independent risk factor for a spectrum of adverse outcomes, including AKI, myocardial injury, and postoperative delirium [22, 23]. Notably, cardiovascular events and AKI are leading contributors to the high 30-day mortality observed after non-cardiac surgery, with up to one-third of deaths potentially attributable to perioperative myocardial injury [23]. Consequently, optimizing intraoperative hemodynamics is paramount for improving outcomes in this vulnerable geriatric population [24].

General anesthetic agents induce vasodilation and reduce systemic vascular resistance, compromising cardiovascular compensatory mechanisms [25]. This is particularly detrimental in older patients with diminished physiological reserve and impaired autoregulation. Evidence consistently demonstrates that blood pressure deviations exceeding 30% from baseline are associated with prolonged recovery and increased mortality [26, 27]. This underscores the limitations of a one-size-fits-all approach using fixed thresholds (e.g., MAP < 65 mmHg or SBP < 90 mmHg) and supports the rationale for individualized targets based on preoperative baseline values.

In the previous study, Futier et al. [15] demonstrated that individualized SBP management during major abdominal surgery reduced postoperative organ dysfunction. We hypothesize that an individualized perfusion pressure management strategy, guided by baseline blood pressure and initiated preemptively before hypotensive events, may improve tissue oxygenation and microcirculation in older hip fracture surgery patients, thus mitigating multi-system ischemic injury.

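### Extracting the continuous arterial pressure only every 5 minutes is too coarse for a secondary outcome that counts any hypotension with no minimum duration

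*Protocol article*

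**What the plan says.** All references are to the protocol article.

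- *Intraoperative monitoring* gives every patient a "radial arterial catheter under local anesthesia for continuous blood pressure monitoring". The pressures and heart rate "will be recorded electronically, with values extracted every" 5 minutes for the analysis. It does not say whether an extracted value is a spot reading or a summary of the preceding interval.
- *Anesthesia induction and intervention* gives the individualized arm "a continuous peripheral intravenous infusion of norepinephrine", titrated to SBP within 10% of baseline. The standard arm receives "intermittent intravenous boluses of norepinephrine" as rescue, once SBP is below 90 mmHg or more than 30% below baseline. A MAP floor of 65 mmHg applies to both arms.
- *Secondary outcomes* includes "the incidence of intraoperative hypotension" from induction to PACU discharge. An event is SBP below 90 mmHg, a fall of more than 30%, or MAP below 65 mmHg. No minimum duration is stated. Total norepinephrine dose is listed as well.
- *Statistical analysis* names SBP over time as an example of repeated-measures data to be analysed by generalized estimating equations (GEE).
- *Discussion* places the mechanism in stabilizing pressure early, "thereby minimizing exposure to IOH".

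**The concern.** Two stated choices fit poorly together. An event with no minimum duration occurs as soon as the pressure crosses a threshold, but the data kept for analysis would show it only if a crossing coincides with an extraction time. The standard-arm rescue trigger is the same as the SBP part of the outcome definition. A patient could therefore be given a rescue bolus for hypotension and still be scored as never hypotensive, because the fall was corrected between two extracted values.

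A yes/no incidence also records neither depth nor duration, although the hypothesized mechanism is reduced exposure. At stake are the accuracy of one named secondary outcome and the account of why the strategy did or did not work.

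**Working it through.** **The plan's own figure.** The article gives no figure on this point. Its one calculation is the sample size for the primary outcome: 55% vs 30%, two-sided α 5%, power 90%, stated as 82 per group. With pooled variance and no continuity correction:

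n = [1.960·√(2·0.425·0.575) + 1.282·√(0.55·0.45 + 0.30·0.70)]² / 0.25² = 80.1, rounded up to 81.

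This agrees with 82 to within one patient, and power at 82 is 90.7%. No pressure value enters the calculation.

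**Inputs for the check.** The extraction interval S = 5 minutes is from *Intraoperative monitoring*. Episode duration d and the mean number of episodes per patient m are not in the article, so the values below are assumptions. Also assumed: spot readings, onset unrelated to the extraction times, and Poisson episode counts.

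**Capture of one episode:** P = min(1, d/S).

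| d (min) | S = 5 | S = 1 |
|---|---|---|
| 0.5 | 10% | 50% |
| 1 | 20% | 100% |
| 2 | 40% | 100% |
| 3 | 60% | 100% |
| 4 | 80% | 100% |

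**Capture of at least one of k episodes:** 1 − (1 − d/5)^k. With three 2-minute episodes this is 1 − 0.6³ = 78.4%, so 21.6% of such patients would be scored as never hypotensive. With one 2-minute episode, 60% would be.

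**Incidence by arm:** true 1 − exp(−m); seen at 5 minutes 1 − exp(−m·d/5). Each pair is standard vs individualized.

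| Assumed m | Assumed d (min) | True | Seen at 5 min |
|---|---|---|---|
| 3 vs 0.5 | 2 vs 2 | 95% vs 39% (56 points) | 70% vs 18% (52 points) |
| 3 vs 0.5 | 1 vs 1 | 95% vs 39% (56 points) | 45% vs 10% (36 points) |
| 0.92 vs 0.36 | 2 vs 2 | 60% vs 30% (30 points) | 31% vs 13% (17 points) |
| 0.92 vs 0.36 | 1 vs 3 | 60% vs 30% (30 points) | 17% vs 19% (−3 points) |
| 3 vs 2 | 2 vs 2 | 95% vs 86% (9 points) | 70% vs 55% (15 points) |

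In the third row, power for this secondary comparison at 90 per arm falls from 99% to 81%. The difference disappears in the fourth row and widens in the fifth.

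**Time below threshold.** Each reading below a threshold stands for 5 minutes, so the expected total is correct when onset is unrelated to the extraction times. A simulation (120-minute record, mean of three 2-minute episodes) gave a true mean of 5.86 minutes and a 5-minute estimate of 5.90 minutes. The standard deviation rose from 3.3 to 5.3 minutes. Coarse spot sampling therefore biases the any-event incidence but only adds noise to mean time below threshold. By the same reasoning, mean SBP over time should not be biased.

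**The case against.** A reader might infer that the loss falls mainly on the standard arm, that it pulls the observed separation toward zero, and that a null primary result could then not be interpreted. The article does not support this.

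- **Arm-specific loss.** No episode lengths or counts are given for either arm. With equal lengths, the chance of missing an episode is the same in both. Both arms have continuous monitoring and the same MAP floor, so prompt correction is possible in both. Shorter episodes under reactive boluses are plausible but not documented, and the complete loss of separation in the fourth row comes from assuming them.
- **Direction.** The fifth row shows that the coarse grid can widen the difference.
- **Interpretability.** The trial has to show a difference in 7-day organ dysfunction, and that test uses none of these values. The sustained contrast in SBP level between the arms is visible at 5-minute spacing through the GEE analysis. Norepinephrine dose does not depend on the sampling at all, and in the standard arm it partly records treated episodes that the grid would miss. Neither measure fully replaces a hypotension measure: mean SBP does not give time below threshold, and dose differs by design.

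It can also be said that extracted values may be interval summaries, that the incidence may not be derived solely from the 5-minute extract, and that the S2 Appendix, which is not shown, gives more detail on secondary outcomes. These points stand as uncertainty about the size of the effect. An interval minimum, for example, would not lose brief falls. They do not remove the stated rule, which gives 5-minute values as the data for analysis. The absence of exposure summaries from the article is not itself the finding, since an article may leave them to other documents.

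**Conclusion.** The point holds as a limited, inexpensive improvement to one secondary outcome. Under spot readings with random onset, 5-minute extraction misses 80% of 1-minute episodes and 60% of 2-minute episodes, so the reported incidence of hypotension is too low whenever episodes shorter than 5 minutes occur. The comparison between arms may be distorted; its size and direction cannot be settled from the article. The arm-level results illustrate assumed episode patterns and are not estimates for this trial. The primary outcome, its chi-square test and the sample size are unaffected. The loss arises at extraction and is recoverable if the electronic record has been kept at finer resolution.

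**What to change.** 1. Establish at what resolution the electronic pressure record is stored, including for patients already enrolled, and state whether an extracted value is a spot reading or an interval summary.
2. Where the record allows, extract at 1 minute or finer under an artefact rule fixed before the data are examined by arm.
3. Report cumulative minutes and time-weighted average below each threshold already in the outcome definition (SBP below 90 mmHg, more than 30% below baseline, MAP below 65 mmHg), alongside the incidence. Finer extraction removes most of the bias in the incidence; for the time measures its gain is precision.
4. If only 5-minute values survive, report the proportion of readings below each threshold. For spot readings this is unbiased for the mean share of time below threshold, though noisier. State that the incidence is a lower bound.

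The cost is data-management time, since *Data collection and management* routes all data through paper case report forms and a finer extract would need a direct electronic export. Finer resolution also brings more artefact. No new measurement is needed, and treatment does not change.
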